## Abstract

**Background:**

Existing data on COVID-19 disparities among vulnerable populations portend excess risk for lesbian, gay, bisexual, transgender (LGBT) and other persons outside of heteronormative and cisgender identities (ie, LGBT+). Owing to adverse social determinants of health, including pervasive HIV and sexual stigma, harassment, violence, barriers in access to health care, and existing health and mental health disparities, sexual and gender minorities in India and Thailand are at disproportionate risk for SARS-CoV-2 infection and severe disease. Despite global health disparities among LGBT+ populations, there is a lack of coordinated, community-engaged interventions to address the expected excess burden of COVID-19 and public health–recommended protective measures.

**Objective:**

We will implement a randomized controlled trial (RCT) to evaluate the effectiveness of a brief, peer-delivered eHealth intervention to increase COVID-19 knowledge and public health–recommended protective behaviors, and reduce psychological distress among LGBT+ people residing in Bangkok, Thailand, and Mumbai, India. Subsequent to the RCT, we will conduct exit interviews with purposively sampled subgroups, including those with no intervention effect.

**Methods:**

SafeHandsSafeHearts is a 2-site, parallel waitlist-controlled RCT to test the efficacy of a 3-session, peer counselor–delivered eHealth intervention based on motivational interviewing and psychoeducation. The study methods, online infrastructure, and content were pilot-tested with LGBT+ individuals in Toronto, Canada, before adaptation and rollout in the other contexts. The primary outcomes are COVID-19 knowledge (index based on US Centers for Disease Control and Prevention [CDC] items), protective behaviors (index based on World Health Organization and US CDC guidelines), depression (Patient Health Questionnaire-2), and anxiety (Generalized Anxiety Disorder-2). Secondary outcomes include loneliness, COVID-19 stress, and intended care-seeking. We will enroll 310 participants in each city aged 18 years and older. One-third of the participants will be cisgender gay, bisexual, and other men who have sex with men; one-third will be cisgender lesbian, bisexual, and other women who have sex with women; and one-third will be transfeminine, transmasculine, and gender nonbinary people. Participants will be equally stratified in the immediate intervention and waitlist control groups. Participants are mainly recruited from online social media accounts of community-based partner organizations. They can access the intervention on a computer, tablet, or mobile phone. SafeHandsSafeHearts involves 3 sessions delivered weekly over 3 successive weeks. Exit interviews will be conducted online with 3 subgroups (n=12 per group, n=36 in each city) of purposively selected participants to be informed by RCT outcomes and focal populations of concern.

**Results:**

The RCT was funded in 2020. The trials started recruitment as of August 1, 2021, and all RCT data collection will likely be completed by January 31, 2022.

**Conclusions:**

The SafeHandsSafeHearts RCT will provide evidence about the effectiveness of a brief, peer-delivered eHealth intervention developed for LGBT+ populations amid the COVID-19 pandemic. If the intervention proves effective, it will provide a basis for future scale-up in India and Thailand, and other low- and middle-income countries.

**Trial Registration:**

ClinicalTrials.gov NCT04870723; https://clinicaltrials.gov/ct2/show/NCT04870723

**International Registered Report Identifier (IRRID):**

DERR1-10.2196/34381

## Introduction

### Background

As of September 30, 2021, India reported 33,739,980 COVID-19 cases and 448,062 deaths [1], and Thailand [2] reported 1,603,475 cases and 16,727 deaths [3,4]. In India, the vast informal workforce, poverty, food insecurity, and an underfunded health care system make projections difficult [5]. Thailand faces similar socioeconomic challenges but on a lesser scale. World Bank [6,7] data reveal that India (0.9/1000) and Thailand (0.8/1000) have nearly 3-fold lower ratios of physicians per capita compared with those of the United States and Canada (both 2.6/1000), with a 5-fold lower ratio of hospital beds in India (0.5/1000) compared with those of the United States (2.9/1000), Canada (2.5/1000), and Thailand (2.1/1000). These data indicate serious health care system challenges amid unknown third and fourth waves of infections and emerging variants of concern [8].

Sexual and gender minorities in India and Thailand, as in many contexts, face pervasive HIV and sexual stigma, harassment, violence, and barriers in access to health care [9-15]. In India, national HIV prevalence among men who have sex with men (MSM) and transgender people is 20-fold higher than that of the general population [16-18]. Depression and alcohol dependence incidence is 5-fold higher among lesbian, gay, bisexual, and transgender (LGBT) people than that among the general population [19-21]. Thailand has a 10-fold higher HIV prevalence among MSM versus the general population [22]. Limited research indicates that depression among LGBT adults is ~10-fold higher than that of the general population [23,24]. High rates of suicidal ideation and substance use have been documented among transgender people [25,26], lesbian women [27,28], MSM [29,30], and LGBT youth [31].

The ongoing pandemic along with various forms of lockdowns and stay-at-home orders in India and Thailand amid new waves of COVID-19 pose particular threats to LGBT and other persons outside of heteronormative and cisgender identities (LGBT+) populations [5,32]. Existing data on COVID-19 disparities among vulnerable populations [33,34] portend an excess risk for LGBT+ people. Mental health challenges due to public health–recommended protective measures (eg, masking, physical distancing) [35], stay-at-home orders, and community-based organization (CBO) closures threaten excess risks for LGBT+ people compounded by stigma and related stress [36,37]. Social and structural vulnerabilities among LGBT+ people that are associated with existing mental health disparities are likely to be exacerbated due to the trauma and social isolation of the pandemic [38], including increases in depression, anxiety, and loneliness [35,39-42].

Adverse social determinants of health [43] (SDOH), including unstable housing, marginal employment, and discrimination in health care, impact the ability to enact physical distancing, work from home, and access testing [33,35]. LGBT+ people, who are more vulnerable owing to adverse SDOH [38,44-48], are among the populations at excess risk, along with people living with HIV [49], ethnic and racial minorities [31], and immigrants and refugees [31,50]. The gendered impacts of the pandemic, including women's disproportionate responsibilities for informal care within families and employment on the frontlines of health care [51], also intersect with these other vulnerabilities [52]. Populations in low- and middle-income countries (LMICs), including LGBT+ people in particular, face risks exacerbated by structural challenges and lack of human rights protections [5,53].

Despite pervasive global health disparities among LGBT+ populations, adverse SDOH [54-56], and lack of human rights protections [32,57], there is a lack of coordinated, community-engaged responses to address the expected excess burden of COVID-19 and public health–recommended protective measures. Public health responses and communications for LGBT+ communities are impeded by lack of LGBT+ community engagement, along with lack of data on health disparities and community needs in the pandemic. Lessons learned from Ebola, H1N1 influenza, and SARS [58,59] indicate that engaging vulnerable communities and building trust are crucial to public health communication and responses [58-61]. With pandemic planning typically framed around the traditional nuclear family and stereotypical gender role assumptions [58], public health–recommended measures often overlook LGBT+ people with different living configurations than those of heterosexual, cisgender people: living with same-gender partners/spouses, friends, hostile families, or alone. This compounds vulnerabilities due to social isolation, and lack of social support and safety [58,62]. Undifferentiated public health responses can exacerbate mistrust among vulnerable communities due to existing disparities, fueling loss of confidence in public health communications [58,59] in a broader context of rampant COVID-19 misinformation [63].

Some restrictions on rights are justified in response to a public health emergency. Nevertheless, as reported by Human Rights Watch [64], UNAIDS (Joint United Nations Programme on HIV/AIDS) [65], the Office of the United Nations High Commissioner for Human Rights [66], and the media [67,68], government emergency powers in response to COVID-19 have led to abuses against LGBT+ people worldwide. These include housing discrimination, evictions, and police brutality against transgender people in India [67]; disproportionate job loss and lack of access to government subsidies for LGBT+ people in Thailand and India, many of whom are marginalized from the mainstream workforce [42]; and exacerbation of sexual and HIV stigma [65,66].

In sum, heightened vulnerability among LGBT+ populations in the COVID-19 pandemic may result from existing health disparities amid ongoing adverse SDOH, compounded by human rights violations and social-structural constraints on enacting public health–recommended protective measures. Yet, public health responses largely do not address LGBT+ vulnerabilities. Extensive evidence supports the acceptability [36,69] and effectiveness of eHealth interventions with LGBT+ and other vulnerable populations in increasing health knowledge and preventive behaviors, and reducing psychological distress [70,71]. Our World Health Organization (WHO)-recommended approach based on community engagement [72] in intervention development, capacitation of CBOs, and cogovernance by trusted CBO partners supports the feasibility, acceptability, and scalability of the intervention [60,73]. The proposed #SafeHandsSafeHearts intervention aims to support LGBT+ individuals amid the pandemic and to advance the broader pandemic response for LGBT+ populations.

### Research Questions

This study addresses the following research questions: What are the needs and challenges faced by diverse LGBT+ people in India and Thailand in the COVID-19 pandemic? What is the level of COVID-19 knowledge, public health–recommended protective behaviors, and psychological distress? Will a brief, tailored, peer-led eHealth intervention increase COVID-19 knowledge and protective behaviors, and reduce psychological distress among LGBT+ people?

### Specific Objectives

The specific objectives of the study are to (1) increase knowledge about COVID-19 transmission, risk, and public health–recommended protective behaviors among diverse LGBT+ persons in India and Thailand; (2) increase public health–recommended protective behaviors, including handwashing, physical distancing, and wearing masks; and (3) reduce pandemic-related psychological distress (anxiety, depression, social isolation/loneliness).

## Methods

### Ethics Approval and Consent to Participate

Ethics approvals have been received from the University of Toronto Research Ethics Board (RIS Protocol: 39769); the Humsafar Trust Institutional Review Board (Protocol: HST-IRB-51-06/2021); and the Institutional Review Board of the Faculty of Medicine, Chulalongkorn University (Protocol: 272/64).

### Study Design

We use a sequential quantitative-qualitative mixed methods design [74]. We will implement a 2-site, parallel waitlist-controlled randomized controlled trial (RCT) to test the efficacy of a 3-session, peer counselor–delivered eHealth intervention to increase COVID-19 knowledge and protective behaviors, and decrease pandemic-related psychological distress. The immediate versus waitlist allocation ratio is 1:1. We conducted a formative intervention development phase with LGBT+ individuals in Toronto to pilot test and refine the online study infrastructure (participant eligibility screening, randomization, survey programming and administration, databases, and dashboard interface for tracking and monitoring) and peer counselor training before rollout in the other 2 sites. All study materials were culturally and contextually adapted through consultation with experts in each site, pilot-tested among individuals from locally eligible study populations, and then revised before implementation.

The immediate intervention group to be enrolled over a 2-month period will complete the 3-session biweekly intervention from August to October 2021. The randomized waitlist control group will crossover to receive the intervention from October to December 2021, after the immediate group finishes. Waitlist control groups, often used in psychosocial interventions [75], avert ethical problems with no-treatment controls, particularly with groups that experience health disparities, moreover amid a pandemic, and also avoid alienating the community.

### Sample Size Calculations

The sample size was calculated based on power to detect significant differences in 3 primary outcomes: proportion of participants with: (1) accurate COVID-19 knowledge, (2) consistent public health–recommended handwashing behaviors, and (3) pandemic-related psychological distress. Given baseline differences in the two countries, we first describe the detailed power analysis for India, where (1) COVID-19 knowledge ranges from 18.2% (fever a major symptom) to 43.0% (highly contagious) [76], and (2) a national survey [77] estimated that 35.8% of the population wash their hands with soap and water. Our baseline estimates are 40% for knowledge and 36% for handwashing (proxy for 3 protective behaviors). A 30% increase postintervention attains clinical/public health significance [78] and a substantial effect size. For (3) psychological distress (depression, anxiety, social isolation), we use a baseline depression rate of 50% (based on a systematic review [19]) as a proxy, with an expected 30% reduction [79]. Using Stata-16, the required sample size to detect significant differences between the waitlist control and immediate-intervention groups, with power of 80%, α of .05 for the 95% CI, and a two-tailed test, ranged from 78 to 86. Assuming 20% attrition, the final sample size was increased to 103 per group (cisgender men, cisgender women, transgender and gender nonbinary people) with power to detect significant differences in each of the 3 groups, for a total sample of 309 in Mumbai.

Using published prevalence of primary outcomes and estimated effect sizes based on similar in-country interventions, we estimated a sample size of 309 for Bangkok [23,28,80-82]. Thus, the trial is powered to detect overall (and by city) sex and gender differences in the primary outcomes (COVID-19 knowledge, protective behaviors, and psychological distress) and the efficacy of the intervention [83].

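### The 103 per gender group multiplies by 1.2 where it should divide by 0.8, so 20% attrition narrowly misses 80% power for two of three planning outcomes; the 30% effects need stating as percentage points

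*Protocol article*

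**What the plan says.** The calculation is in the protocol article, Methods, Sample Size Calculations, and is worked in detail for India only.

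- **Baselines.** "Our baseline estimates are 40% for knowledge and 36% for handwashing (proxy for 3 protective behaviors"), and for distress, "we use a baseline depression rate of 50" percent.
- **Effects.** For knowledge and handwashing: "A 30% increase postintervention attains clinical/public health significance". For depression, standing in for distress: "with an expected 30% reduction". Neither sentence says whether the 30% is in percentage points or relative to baseline.
- **Requirement before attrition.** "with power of 80%, α of .05 for the 95% CI, and a two-tailed test, ranged from 78 to 86".
- **Attrition.** "Assuming 20% attrition, the final sample size was increased to 103 per group". The groups named there are the three gender strata (cisgender men, cisgender women, transgender and gender nonbinary people), not the randomised arms. Three times 103 gives the 309 for Mumbai, and the section claims power within each of the three strata.
- **Allocation** (Study Design). "The immediate versus waitlist allocation ratio is 1:1".

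The Statistical Analysis Plan section relies on this calculation when it says the sample size is powered for the a priori gender subgroup analyses. Bangkok also gets 309, from its own prevalences and effect sizes, which the article does not list.

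**The concern.** To end with 86 analysable participants after losing 20%, one divides by the retained fraction, 0.8. Multiplying by 1.2 falls short, because 20% of the larger enrolled number is then lost. The figure of 103 looks like the product of multiplication. If so, the 80% power claimed within each gender group does not hold under the protocol's own attrition assumption.

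The effect size is also not identified by the text. A 30% change in a quantity already expressed in percent can mean two very different things, and the required sample differs several-fold between them. At stake is the reading of the gender-group results: someone who takes the 30% as relative could treat a null result in one group as evidence against an effect that the group was never sized to detect.

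**Working it through.** **Inputs.** Baselines 40%, 36% and 50%; effect 30%, up or down; two-sided α = .05; power 80%; attrition 20%; 103 per gender group (all from Sample Size Calculations); 1:1 allocation (Study Design).

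**Step 1: reproduce the stated 78 to 86.** Standard two-proportion formula with pooled variance under the null, no continuity correction, p̄ = (p₁ + p₂)/2:

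n per arm = [1.960·√(2p̄(1−p̄)) + 0.842·√(p₁(1−p₁) + p₂(1−p₂))]² / (p₁ − p₂)²

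Taking 30% as percentage points:

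| Outcome | p₁ → p₂ | n per arm | rounded up | both arms |
|---|---|---|---|---|
| Knowledge | 40% → 70% | 41.97 | 42 | 84 |
| Handwashing | 36% → 66% | 42.39 | 43 | 86 |
| Depression | 50% → 20% | 38.48 | 39 | 78 |

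The range 78 to 86 is matched exactly, as the total over both arms within one gender group.

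**Step 2: try the relative reading.** Taking 30% of the baseline value:

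| Outcome | p₁ → p₂ | n per arm, rounded up | both arms |
|---|---|---|---|
| Knowledge | 40% → 52% | 270 | 540 |
| Handwashing | 36% → 46.8% | 326 | 652 |
| Depression | 50% → 35% | 170 | 340 |

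These are nowhere near 78 to 86. One-sided and continuity-corrected versions of the relative calculation do not come near either. A one-sample test on the relative depression effect gives about 85, but the same test gives about 132 and 159 for the other two outcomes, and the planned comparison has two arms. The calculation therefore used percentage points.

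**Step 3: attrition.**

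- 86 × 1.2 = 103.2, the stated 103.
- 86 / 0.8 = 107.5, that is 108 per gender group and 3 × 108 = 324 per city.
- 103 × 0.8 = 82.4, so about 82 remain, or 41 per arm. This is below the 86 for handwashing and the 84 for knowledge, and above the 78 for depression.
- Largest loss that 103 can absorb: 1 − 86/103 = 16.5% (handwashing), 1 − 84/103 = 18.4% (knowledge), 1 − 78/103 = 24.3% (depression).

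**Step 4: power after 20% attrition.** Power = Φ{[|p₁ − p₂|·√n − 1.960·√(2p̄(1−p̄))] / √(p₁(1−p₁) + p₂(1−p₂))}, with n per arm:

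| Outcome | Gender group, n = 41 | Mumbai as a whole, n = 123.6 |
|---|---|---|
| Handwashing, 36% → 66% | 78.6% | 99.8% |
| Knowledge, 40% → 70% | 79.0% | 99.8% |
| Depression, 50% → 20% | 82.5% | 99.9% |

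The city figure uses 309 × 0.8 = 247.2, or 123.6 per arm. Carrying 41.2 instead of 41 per arm in the gender groups gives 78.8%, 79.2% and 82.7%.

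**Step 5: differences detectable at 80% power after attrition, Mumbai baselines.** Solving the same expression for p₂:

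- per gender group (41 per arm): 30.5 points for handwashing, 30.3 for knowledge, 29.2 for depression;
- Mumbai as a whole (123.6 per arm): about 17.5 to 18 points;
- both cities (about 247 per arm): about 12.5 points, but only if Mumbai's baselines are assumed for Bangkok.

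**The case against.** The strongest reply is that the slip hardly matters. The shortfall is 1.4 points of power for handwashing and 1.0 for knowledge, depression stays above 80%, and the whole effect lies within single gender groups in one city. The inputs are rougher than that: handwashing is a proxy for three behaviours, depression is a proxy for distress, and the knowledge baseline of 40% comes from a literature range of 18.2% to 43.0%. All of this stands, and it limits the weight of the point. It does not make the statement correct, because the article claims 80% power under its own 20% attrition and its own figures do not give it.

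A second reply is that the 30% is an ambiguity and not a calculation error. That also stands. A reader might infer that the trial was planned for a relative 30% change and is therefore badly underpowered: on that reading 103 per gender group, less 20%, would give roughly 17–28% power, and one city 41–67%. The document does not support that inference. It does not say relative, and its stated range reproduces only with percentage points. Those low figures describe a reading that the plan did not use; they show why the wording should be settled, not the size of a defect.

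Third, the inputs shown are for Mumbai. Bangkok's are not given, so nothing here shows that Bangkok's power claim is met or missed.

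**Conclusion.** The attrition adjustment is wrong as written. The number needed is 108 per gender group (324 per city) against the stated 103 (309). Under the protocol's own assumptions, power in each Mumbai gender group is 78.6%, 79.0% and 82.5%, so 80% is narrowly missed for two of three planning outcomes. The comparison in Mumbai as a whole is not affected, with over 99% power for the planned effects.

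The effect size is unclear in the text but not in the calculation: it is 30 percentage points, which amounts to a relative rise of 83% in handwashing (30/36) and a relative fall of 60% in depression (30/50). A relative 30% change would have needed 340 to 652 per gender group.

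These results assume the pooled two-proportion test without continuity correction, which matches the stated range exactly, equal arms, and attrition equal in both arms.

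**What to change.** Correct the wording of Sample Size Calculations; enrolment need not change.

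1. State that 103 per Mumbai gender group gives about 79–83% power at 20% attrition, and that 80% for all three outcomes is kept only up to 16.5% loss.
2. Write the effects as percentage points: knowledge 40% to 70%, handwashing 36% to 66%, depression 50% to 20%. Say that 78 to 86 is the two-arm total per gender group.
3. Give the Mumbai differences detectable at 80% power after 20% attrition: about 29 to 30.5 points per gender group and about 17.5 to 18 points for the city.
4. Give a both-cities figure (about 12.5 points) only if it is labelled as assuming Mumbai's baselines in Bangkok.

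The cost is a few sentences and a stated power that is slightly less favourable.

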### Statistical Analysis Plan

Intervention efficacy will be assessed by comparing data from the second preintervention baseline survey from the waitlist control with postintervention data from the immediate intervention group. The *χ^2^* test for unadjusted analyses and logistic generalized estimating equations (GEEs) for adjusted analyses [130] will be used to assess dichotomous primary outcomes (COVID-19 knowledge, protective behaviors, psychological distress). Sensitivity analyses will use composite scores of primary outcomes with independent-samples *t* tests for unadjusted analyses and GEEs (Gaussian or Poisson) for adjusted analyses. To assess if intervention efficacy is sustained, waitlist control data from the second preintervention survey will be compared with intervention group follow-up data. We will use intention-to-treat analyses and also report per-protocol analyses [131]. In addition to analyses of efficacy for LGBT+ people as a whole, the sample size is powered for a priori subgroup analysis (cisgender gay/bisexual men, cisgender lesbian/bisexual women, transgender and gender nonbinary people). We will assess if intervention effects on protective behaviors are mediated by increases in knowledge, self-efficacy, perceived vulnerability, and decreases in conspiracy theories and psychological distress, and if the effects on psychological distress are mediated by resilience.

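### The claim that the trial is powered for sex and gender differences does not follow from a calculation that sizes only the arm comparison within one sex/gender group

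*Protocol article*

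**What the plan says.** The Sample Size Calculations section describes one calculation in detail, for Mumbai. What it derives is "the required sample size to detect significant differences between the waitlist control and immediate-intervention groups". The result is a range of 78 to 86, at 80% power and a two-sided significance level of 0.05. The inputs are baseline rates ("Our baseline estimates are 40% for knowledge and 36% for handwashing (proxy for 3 protective behaviors"), an effect ("A 30% increase postintervention attains clinical/public health significance"), and for distress a 50% baseline depression rate with an expected 30% reduction. After a 20% attrition allowance the figure becomes 103 for each of cisgender men, cisgender women, and transgender and gender nonbinary people, "with power to detect significant differences in each of the 3 groups". That makes 309 in Mumbai. Bangkok is also given 309, without its rates.

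The section then closes with "Thus, the trial is powered to detect overall (and by city) sex and gender differences in the primary outcomes", and names the efficacy of the intervention as a second item in the same sentence. The Statistical Analysis Plan section adds that "the sample size is powered for a priori subgroup analysis" by the same three groups. It names chi-square tests and logistic GEEs for the dichotomous primary outcomes.

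**The concern.** Power to detect an arm difference inside each group is a different quantity from power to detect a difference between groups, whether in outcome level or in intervention effect. The closing sentence moves from the first to the second with the word 'Thus'. Because it lists efficacy separately, the sex and gender part cannot simply be another name for the arm comparison.

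At stake is how the subgroup results are read. Sex/gender is the stratification factor, and the article presents subgroup analysis as a priori and powered. A reader told that the trial can detect sex and gender differences, by city as well as overall, may take a non-significant between-group comparison as evidence that the groups respond alike. For differences in effect within one city, the sample does not support that reading.

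**Working it through.** **Inputs.** From the protocol article: control rates 40% (knowledge), 36% (handwashing) and 50% (depression); effect 30%; 80% power, two-sided 0.05; 1:1 allocation; 103 per sex/gender group per city; 20% attrition. Hence 103 × 0.8 = 82.4 evaluable per group per city, or 41.2 per arm. With full retention it is 51.5 per arm. With both cities it is 82.4 evaluable per arm per group.

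Three further assumptions are not in the document. The effect in the comparison group is taken as zero, with half the full effect as the alternative. Bangkok is given Mumbai's rates for the pooled figures. Effects are measured as risk differences.

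**Step 1: reproduce the stated figure.** Two-proportion formula with pooled variance under the null and no continuity correction:

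n per arm = [1.96 √(2p̄(1−p̄)) + 0.84 √(p₁(1−p₁) + p₂(1−p₂))]² / (p₁−p₂)²

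| Outcome | Rates | Per arm | Both arms |
|---|---|---|---|
| Knowledge | 40% to 70% | 42 | 84 |
| Handwashing | 36% to 66% | 43 | 86 |
| Depression | 50% to 20% | 39 | 78 |

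This matches 78 to 86. That range is therefore the two-arm total in one sex/gender group, for a 30-percentage-point arm difference. A relative 30% would need 170 to 326 per arm and does not fit. At 41.2 evaluable per arm, power for this within-group comparison is 79.2%, 78.8% and 82.7%.

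**Step 2: difference in intervention effect between two groups, one city.** With D the difference between two risk differences:

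SE = √[Σ p(1−p) / n] over the four arm-by-group cells; power = Φ(D/SE − 1.96)

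Handwashing, full effect against none, n = 41.2: Σ p(1−p) = 3(0.36 × 0.64) + 0.66 × 0.34 = 0.9156; SE = √(0.9156/41.2) = 0.149; 0.30/0.149 − 1.96 = 0.05; power 52.1%.

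Handwashing, full effect against half (36% to 66% against 36% to 51%): Σ p(1−p) = 0.9351; SE = 0.151; 0.15/0.151 − 1.96 = −0.96; power 16.7%.

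| Scenario (range over the three outcomes) | Full vs none | Full vs half |
|---|---|---|
| One city, 20% attrition (41.2 per arm per group) | 51.5-52.3% | about 17% |
| One city, full retention (51.5) | 61-62% | 20-21% |
| Both cities, 20% attrition (82.4) | 81-82% | 29-30% |

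On the logit scale, the one-city full-versus-none figures after attrition are 49%, 48% and 55%. For 80% power at a 30-point difference in effect, 80 to 82 evaluable per arm per group are needed, about twice what one city provides.

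**Step 3: difference in outcome level between two groups, one city.** This uses the Step 1 formula, with whole groups compared and the control rates as reference.

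| Level difference | 82.4 vs 82.4 | 103 vs 103 |
|---|---|---|
| 30 points | about 98% | over 99% |
| 20 points | 73-75% | 82-84% |
| 15 points | 49-50% | 58-59% |
| 10 points | about 25% | 30-31% |

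Solving for 80% power gives 19 to 20 points with all 103, and 21 to 22 points after 20% attrition.

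**The case against.** The strongest reply is that the sentence speaks of differences in the primary outcomes and does not mention effect modification. One of the article's research questions asks about levels of knowledge, behaviours and distress. Read that way, a 30-point difference between groups has about 98% power per city, and the sentence is imprecise rather than badly wrong. This stands as a possible reading, which is why both readings are sized above. It does not rescue the inference: no level difference is named, and a 10-point difference has only 25 to 31% power per city.

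Four stronger conclusions might be inferred, and the documents do not support them.

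- **That 52% is a ceiling.** It depends on 20% attrition, the risk-difference scale and no effect in the second group. Full retention gives 61-62%. The sentence also says overall, and the pooled figure of about 81% meets the usual standard for this extreme case.
- **That the subgroup power wording elsewhere is wrong.** "with power to detect significant differences in each of the 3 groups" and "the sample size is powered for a priori subgroup analysis" are both fair as statements about arm differences within a group, where power is 79-83%.
- **That the plan rests on separate pass/fail tests by group.** The Statistical Analysis Plan section does not prescribe them and does not exclude an interaction term.
- **That all three groups must reach significance.** With a common 30-point effect, all three would do so in one city about half the time (0.788³ = 0.49 to 0.827³ = 0.57). The protocol never sets that requirement, so this is no failing of the plan.

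**Conclusion.** The point holds for one sentence. The closing claim of the Sample Size Calculations section is unsupported: the calculation behind it sizes only waitlist versus immediate intervention within one sex/gender group.

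Read as a claim about differences in effect, it fails by city even when one group has the full effect and another none, with or without attrition. Pooled over cities it is met only for that extreme contrast, and only if Bangkok's rates resemble Mumbai's, which the article does not give. Read as a claim about outcome levels, it holds for differences of roughly 20 points or more, and the text should say so.

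The main efficacy comparison is not in question. With 309 × 0.8 / 2 = 123.6 evaluable per arm per city, a 30-point arm difference has over 99% power. The consequence is confined to how between-group results are described and interpreted.

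**What to change.** In the Sample Size Calculations section, restate the closing sentence as power for arm differences of about 30 percentage points within each sex/gender group. Then either drop the between-group claim, or state whether levels or effects are meant, the size of difference, and its power per city and pooled, with the Bangkok rates assumed.

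For any statement that efficacy differs by sex/gender, use an arm-by-sex/gender interaction in the planned GEE on both cities, and report group-specific effects with confidence intervals as estimates. The power wording in the Statistical Analysis Plan section, and the phrase about each of the three groups, can stay as within-group statements.

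The cost is a less favourable power statement and one added interaction analysis. No extra participants are needed and the overall efficacy analysis does not change.
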